### Interim analyses {21b}

N/A: There will not be interim analyses.

### Methods for additional analyses (e.g. subgroup analyses) {20b}

N/A: No subgroup analyses or adjusted analyses will be performed because they are not part of the planned analyses for this study. The primary analysis is sufficient to address the research question.

### Methods in analysis to handle protocol non-adherence and any statistical methods to handle missing data {20c}

An intention-to-treat analysis will be performed, and the last available measurement will be used when data were lost due to dropout. To address missing data, the multiple imputation method will be employed. For participants randomized to the intervention group who do not adhere to the intervention, a per-protocol analysis will also be performed to assess the impact of non-adherence on the study outcomes.

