### Additional consent provisions for collection and use of participant data and biological specimens {26b}

If a patient withdraws consent, their data will be removed from the database and will not be used for analysis. In the case of study discontinuation, data may be retained if authorized by the patient. In such cases, primary and secondary outcomes will be assessed at the date of discontinuation.

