### Outcomes {12}

All assessments were completed by an experienced occupational therapist who was blind to the participants' group assignments. Assessments were conducted before the start of the intervention (pre-training), after 4 weeks of treatment (post-training), and at the 1-month follow-up (follow-up).

The primary outcome of this study was swallowing function, assessed using the Toronto Bedside Swallowing Screening Test (TOR-BSST) and the Functional Oral Intake Scale (FOIS). The Toronto Bedside Swallowing Screening Test (TOR‐BSST) is the best performing water swallow screening tool [21] with a sensitivity of 91.3%, a negative predictive value of 93.3% in the acute phase and 89.5% in the recovery phase [22]. TOR-BSST has shown to be more convenient and cheaper in bedside screening compared to the gold standard method of simultaneous videofluoroscopy (VFSS), which is an invasive assessment. Due to the limitations of the experimental site, we chose TOR-BSST as the assessment tool for dysphagia. FOIS consists of a 7-point scale, with level 1 indicating completely impaired oral intake and level 7 indicating complete oral intake regardless of food concentration or type [23].

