### Sample size {14}

The sample size was calculated from a previous study conducted by Park et al. [29] in dysphagia patients, which measured patient swallowing function on the Functional Oral Intake Scale (FOIS), with mean of 5.40 and 4.40, SDs of 1.70 and 0.80 for the intervention and control groups, respectively. For a significant level of 0.05 and power of 90%, 31 participants were estimated in each group (62 participants). Finally, to avoid loss of power due to potential dropout, the sample size was increased by 20% for each group, resulting in a total number of participants of *N* = 78. The sample size was estimated using G-Power 3.1 [30].

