## Statistical methods

### Statistical methods for primary and secondary outcomes {20a}

An intention-to-treat analysis will be performed, and the last available measurement will be used when data were lost due to dropout. Statistical analysis will be performed using SPSS 29.0. Statistical significance of all outcome variables will be established at *P* < 0.05.

All continuous data will be tested for normality, and nonparametric tests will be used for non-normally distributed data. Data conforming to normal distribution will be expressed as mean ± standard deviation (SD), and data with non-normal distribution will be expressed as median (interquartile range).

Comparisons of continuous data of two groups at the same time will be analyzed using independent samples t tests or rank sum tests, and comparisons of two groups of rates will be performed using chi-square test or Fisher exact test [31].

Comparison of continuous data trends over time between different groups at different times, if data normality is present, we will perform a series of repeated measures analysis of variance (ANOVA) for each outcome measure to assess differences between time (4 weeks and 1 month post) and between study groups, as well as interactions between time and study groups. For these analyses, the assumptions of sphericity and homogeneity of variances are tested using Mauchly and Levene tests [32]. If the assumption of sphericity is violated, the Huynh–Feldt correction is applied [32].

If the normality assumption is not met, the linear mixed model will be used for analysis, the comparative analysis at each time was performed using the nonparametric statistical Mann–Whitney U test and its own control two-way comparison using the nonparametric statistical Kruskal–Wallis rank sum test [33].

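### Carrying the last value forward is the stated rule for dropout, multiple imputation is added without scope or rank, and carrying forward can bias the comparison of swallowing function

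*Protocol article*

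**What the plan says.** The main statistical section, Statistical methods for primary and secondary outcomes {20a}, gives one rule: "An intention-to-treat analysis will be performed, and the last available measurement will be used when data were lost due to dropout". Multiple imputation is not mentioned there.

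The section on non-adherence and missing data {20c} repeats that rule and goes straight on to a second method: "measurement will be used when data were lost due to dropout. To address missing data, the multiple imputation method will be employed". No sentence limits multiple imputation to gaps other than dropout, and none calls either method primary or sensitivity.

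Three other places bear on the point:

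- Outcomes {12} schedules assessments at baseline, after 4 weeks of treatment and at a 1-month follow-up, with none between baseline and week 4.
- The consent section {26b} covers patients who discontinue and allow their data to be kept: "In such cases, primary and secondary outcomes will be assessed at the date of discontinuation".
- Sample size {14} allows for 20% dropout in each group, giving 78 patients.

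**The concern.** There are two problems.

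The first is the text. Two methods are prescribed, their scopes overlap and neither is ranked. A single dropout value could be filled by either, and on this document alone the choice could be made after the results are known.

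The second is the dropout rule itself. Baseline is the only scheduled value before week 4, so carrying forward gives a patient who leaves during treatment an improvement of zero, unless a discontinuation assessment was obtained. Both arms train actively for four weeks and also receive usual care, so zero change is an implausible default. The filled-in value is then analysed as if it had been observed.

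The comparison of FOIS scores, a primary outcome, is at stake. Carrying forward can create a difference where none exists, or shrink a real one.

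**Working it through.** **Inputs from the protocol.** FOIS figures from Sample size {14}: "with mean of 5.40 and 4.40, SDs of 1.70 and 0.80 for the intervention and control groups, respectively"; significance level 0.05; power 90%; 31 per group; 20% dropout allowance; 78 in total.

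**Assumed inputs (not in the protocol).** Mean gains from baseline to week 4; dropout by arm; baseline to week-4 correlation 0.6 and a common SD of 1.33 in the simulation; dropout at random within arm, so that leavers would have gained as much as stayers; no discontinuation assessment obtained.

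**Step 1: the plan's own figure.** Pooled SD = √((1.70² + 0.80²)/2) = 1.3285, so d = 1.00/1.3285 = 0.753. A t-test with one-sided alpha 0.05 and 90% power needs 30.9, hence 31 per group, which reproduces the plan. Two-sided it needs 38.1, hence 39. Then 31/(1 − 0.20) = 38.75, rounded up to 39 per arm and 78 in total, which also reproduces. Two-sided power for a 1.0 difference is 90.7% with 39 per arm and no dropout, and 83.0% with 31 per arm.

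**Step 2: bias at week 4.** Let d be dropout before week 4 and g the mean gain, with E the game arm and C the control arm.

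- Estimate with carrying forward = (1 − dE)·gE − (1 − dC)·gC
- True difference = gE − gC
- Bias = dC·gC − dE·gE

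When both arms gain, the bias favours the game arm only if dC/dE > gE/gC.

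**Step 3: no true effect.**

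| Gain, both arms | Dropout game / control | Bias (FOIS points) |
|---|---|---|
| 1.0 | 20% / 20% | 0.20 − 0.20 = 0 |
| 1.0 | 10% / 25% | 0.25 − 0.10 = +0.15 |
| 1.5 | 10% / 25% | 0.375 − 0.15 = +0.225 |
| 1.0 | 10% / 30% | 0.30 − 0.10 = +0.20 |
| 1.5 | 10% / 30% | 0.45 − 0.15 = +0.30 |

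In a simulation with 39 per arm, the last two rows give a two-sided type I error of about 9% and 14% with carrying forward, against about 5% with multiple imputation.

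**Step 4: the planned 1.0 difference, gains 2 versus 1.**

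| Dropout game / control | Estimate with carrying forward |
|---|---|
| 20% / 20% | 0.80·2 − 0.80·1 = 0.80 |
| 15% / 25% | 0.85·2 − 0.75·1 = 0.95 |
| 10% / 30% | 0.90·2 − 0.70·1 = 1.10 |

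The middle row is biased against the game arm although that arm has less dropout.

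**Step 5: power at 20% / 20%.** Simulated power is about 64 to 65% with carrying forward (estimate 0.80). With multiple imputation it is about 84% (estimate 0.99). A t-test on observed values only, with about 0.80 × 39 = 31 per arm, has 83%. Part of the loss comes from mixing baseline and week-4 values, which adds d(1 − d)g² to each arm's variance: 0.16·4 = 0.64 and 0.16·1 = 0.16, on average 0.40. The SD rises to √(1.33² + 0.40) = 1.47 while the difference falls to 0.80.

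**Step 6: dropout between week 4 and follow-up.** The same formula applies with g replaced by the change after week 4. At 10% / 30% and equal change in both arms, the bias is +0.10 if patients gain another 0.5, zero if they are stable, and −0.10 if they lose 0.5.

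**The case against.** The strongest reply is that the two sentences can be read together: the last value for dropout, multiple imputation for other gaps such as a missed visit or unanswered questionnaire items. The reading is coherent, and it rules out the inference that carrying forward leaves nothing to impute. But the protocol does not state this split. Even if it did, dropout, the one cause of missing data that these sections name and the one the sample size allows for, would still be handled by carrying forward. The reply answers the charge of contradiction but not the bias.

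Four further limits stand:

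- **Direction.** A reader might infer that carrying forward always favours the arm with less dropout, and so inflates the game effect. Step 4 shows that this fails when gains differ.
- **Dropout by arm.** The background expects poor adherence to conventional training, and section {11c} expects high compliance with the game. These statements concern training, and Outcomes {12} measures adherence by sessions completed. A patient who skips sessions can still be assessed at week 4. No dropout rate by arm is given, and the only planned figure is 20% in each group.
- **Discontinuation assessments.** Where one is obtained, it replaces baseline and the week-4 bias is likely to be smaller. The figures above assume none.
- **Reference for power.** It is tempting to set the reduced power against the roughly 91% of 39 complete patients per arm. That charges carrying forward with a loss that dropout causes under any method. The fair reference is about 83%.

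A statistical analysis plan that is not shown may also rank the methods. That would settle the choice, but the protocol's own sentences would still need to agree with it.

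**Conclusion.** The point holds in this form: the protocol prescribes carrying forward for dropout, adds multiple imputation without scope or rank, and the dropout rule can bias the comparison in either direction.

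That two methods are named and neither is ranked rests on the text alone. The sizes rest on assumed gains and dropout. With no true effect, 10% versus 25% dropout and gains of 1.0 to 1.5 points, the spurious benefit is 0.15 to 0.23 points, or 15 to 23% of the planned 1.0 difference. With equal 20% dropout and gains of 2 versus 1, the estimate is 0.80 instead of 1.0, with about 65% power against about 83%. The documents do not show that dropout will differ between arms or that the game arm will be the one favoured.

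**What to change.** In sections {20a} and {20c}, replace carrying forward as the primary handling of dropout with one named method, worded identically in both places. Either of these would serve:

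- multiple imputation, which {20c} already names; or
- a likelihood-based mixed model on all observed data. Section {20a} already mentions a linear mixed model, though only for non-normal data.

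Whichever is chosen should use any assessments made at discontinuation. Last observation carried forward can stay at most as a sensitivity analysis labelled as such. The change should be made before anyone sees outcome data by arm.

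The cost is a few reworded sentences, a little more analysis work and possibly slightly wider confidence intervals. The total of 78 patients does not change.

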### Plans to give access to the full protocol, participant level-data and statistical code {31c}

The project has been made public in clinical trials. The datasets and statistical codes analyzed in this study and the complete study protocol are available from the corresponding author upon reasonable request.

## Oversight and monitoring

### Composition of the coordinating centre and trial steering committee {5d}

This is a study designed, implemented and coordinated by the Hong Kong Polytechnic University. Day-to-day support for the study is provided by the Principal Investigator. The Data Manager is responsible for organizing data collection and ensuring data quality. The study coordinators help with trial registration, collect informed consent, ensure follow-up according to protocol, and address participant concerns. The study team will meet every two weeks throughout the duration of the study. There will be no trial steering committee or stakeholder and public participation meetings. The Hong Kong Polytechnic University Ethics Committee will check the completeness of the study.

### Composition of the data monitoring committee, its role and reporting structure {21a}

Data monitoring committee (DMC) was not specified for this study. This decision was made on the basis that no serious adverse events would occur in this study.

### Adverse event reporting and harms {22}

Adverse events will be documented by the research coordinator. Minor adverse events such as fatigue will be recorded in the adverse event count form. A healthcare staff who is not involved in the study will accompany the participants during their training. Since the use of video games as an intervention method may cause discomfort such as visual fatigue in participants, the study will be stopped and observed immediately when participants experience any discomfort. If the discomfort is not relieved after half an hour, it will be immediately reported to the doctor in charge and relevant treatment will be given. Serious adverse events, such as fractures, and bleeding will be reported immediately to the Health Research Ethics Committee and discussed with the participant's doctor, who will provide medical follow-up if necessary. Participants may withdraw from the trial at any time.

### Frequency and plans for auditing trial conduct {23}

A project management team comprised of the Principal Investigator will meet monthly to review recruitment, project compliance and identify any issues. As the risk of intervention is low, the establishment of an independent data safety monitoring commissioner will not be considered.

### Plans for communicating important protocol amendments to relevant parties (e.g. trial participants, ethical committees) {25}

All substantive modifications to this study will go through a structured communication process. The Principal Investigator (PI) will first inform the sponsor of any proposed modifications. Subsequently, the PI will seek approval from the Ethics Committee and the competent authorities of The Hong Kong Polytechnic University. Once the modification is approved, the PI will immediately notify the participating centers for the modification and provide a copy of the revised proposal, which will be added to the Investigator Site File accordingly. Any deviation from the protocol will be recorded in detail using the breach report form to ensure transparency and accountability. In addition, the protocol in the Clinical Trial Registry will be updated in a timely manner to reflect approved revisions. This comprehensive approach to protocol revision aims to maintain the integrity of the study while keeping all interested parties informed.

### Dissemination plans {31a}

The results of this study will be fully disclosed in the international peer-reviewed journals. Both positive and negative results will be reported. A summary of the results will be presented to the school authorities.

## Patient public involvement

This study did not involve public and patient representatives in the study design. However, after the preliminary development of the video-game system was completed, a total of 19 participants, including health caregivers, patients with dysphagia, and their families, were involved to experience the game and interviewed, providing many informative suggestions for video-game system modifications.

## Discussion

Swallowing training combined with video games may be a more feasible and effective intervention strategy than using usual care alone to improve swallowing function in patients with dysphagia. However, there is no evidence for the role of video-game based swallowing function training. Therefore, this study aims to provide new insights into whether video-game based swallowing function training can be an effective way to enhance swallowing function in patients with dysphagia. This will be the first known longitudinal study to combine a complete swallowing training program with video-game.

Swallowing movements can be understood as nutritional intake and airway blocking movements. In healthy individuals, the food bolus ingested through the mouth is transported through the esophagus to the stomach [34]. There are four consecutive coordinated phases of swallowing: the oral preparation phase, the oral propulsion phase, the pharyngeal phase, and the esophageal phase. The peripheral muscles involved in swallowing movements include the masticatory muscles, facial muscles, suprahyoid muscles, soft palate muscles, pharyngeal muscles, infrahyoid muscles, and intrinsic lingual muscles [35]. In patients with neurological disorders, central nervous system disorders lead to dysfunction and incoordination of the oropharyngeal muscles, and thus patients are likely to have dysphagia [36]. Also, advanced age or weakness of the muscles of the face, palate, and pharynx may increase the odds in developing dysphagia among patients. Therefore, appropriate muscle rehabilitation is a common and effective way to improve the swallowing function of patients.

Video games have deep potential for patient rehabilitation, such as reducing neuromotor impairment [37], improving cognition and attention [38], reducing anxiety and depressive symptoms [39], or managing chronic conditions [40]. Gamification is a useful strategy to achieve effective completion of rehabilitation by combining it with certain therapeutic interventions [41], such as muscle training, and by inspiring patients with points or rewards to increase their participation and motivation. Some serious games or video games for the education of patients with dysphagia have shown positive results [42]. However, to our knowledge, there are no trials that have studied the evaluation of the effectiveness of video-game for rehabilitation in patients with dysphagia for motor purposes.

This randomized controlled trial will not only provide evidence for the immediate effects of swallowing rehabilitation, but also for the short-term effects of video-game by follow-up. This study will help to estimate the variance of primary and secondary outcome indicators, correlations between measurement times, and effects with time. With more accurate sample size calculations, this will help confirm the need for a larger definitive trial targeting dysphagia rehabilitation. It will also determine whether video-game based swallowing function training is a useful intervention strategy for patients with dysphagia.

Although the results of this study may have important implications in the field of dysphagia rehabilitation, there are some limitations. First, the use of video games for training of patients with dysphagia has some requirements for the patients' ability to use a computer or computer configuration. This may result in some families of people with dysphagia not having access to video games. We have kept the computer usage requirements as low as possible, so that patients can simply click on the software and select the game to begin training. Second, blinding participants, carers and people delivering the interventions is very difficult due to the intervention method. We will require participants not to discuss study details with each other and conduct pre-experimental training for implementers to strictly follow experimental protocol details for minimizing the risk of bias. Third, because of the limitations of the study site, we were not able to use the gold standard video fluoroscopic swallowing study (VFSS) as a tool to assess dysphagia. Instead, we used the Toronto Bedside Swallowing Screening Test, which has been proven to have high sensitivity and specificity. This would lead to some limitations in the reliability of the results. Fourth, since we used some questionnaires in the study, this may increase recall bias and Hawthorne effects in participants' questionnaires. We will strictly train questionnaire investigators to require standardized answers to participants' questions in order to reduce participants' self-consciousness.

This randomized controlled trial will examine the effect of video-game based swallowing training on swallowing function, swallowing-related quality of life, and adherence to rehabilitation training in patients with dysphagia. It may provide evidence on swallowing function training, clinical care management, and lifestyle interventions for patients with dysphagia.

## Trial status

The current protocol is version 1 of August 2023. The trial status is currently in the pre-recruitment phase. Recruitment is planned to start in October 2023. Recruitment and trial are expected to be completed by July 2024.

## Data Availability

The final trial data for this protocol can be supplied on request.

## Abbreviations

BMI: Body mass index
CRF: Case report form
DMC: Data monitoring committee
FOIS: Functional oral intake scale
MNA-SF: Mini nutritional assessment short form
RCT: Randomized controlled trial
SD: Standard deviation
SWAL-QOL: Swallowing quality of life
TOR-BSST: Toronto bedside swallowing screening test
TURF: Task, user, performance, and function
VFSS: Video fluoroscopic swallowing study
